### Primary outcome analysis

The primary outcome measure is the VHI total score at 3 months. A linear regression model will be used to estimate differences in the VHI total score at 3 months between the two arms of interest, with the VHI baseline score and the minimisation variables age and severity of PD (Hoehn and Yahr) included in the model as covariates.

### Secondary outcome analyses

The majority of the secondary outcome measures (e.g. PDQ-39) are continuous measurements and will be analysed in a similar way to that described for the primary analysis: a linear regression analysis adjusting for relevant baseline score and all of the minimisation variables (baseline VHI, age and severity of PD). As per the primary outcome, the primary analysis for the secondary outcomes will be based on the 3-month data.

To assess whether any treatment effect is maintained, participant- and carer-completed questionnaires are also being collected at 6 and 12 months post randomisation. Data collected at 6 and 12 months will be analysed using the same methods as described above. Further analysis using a repeated measures model will also be performed using all data over the 3-, 6- and 12-month assessment points.

A global rating scale (Transition item) will be completed by the participant and carer separately at the 3-month time point. This data will be used to calculate an MCID for the VHI in this population.

Adverse events and safety data will be summarised descriptively by treatment arm, and the number of events and percentage of participants experiencing any AE reported. It is not expected that there will be many AEs as a result of the intervention, but the number of participants reporting an AE will be compared using a chi-squared test, with relative risks and 95% confidence intervals reported (if appropriate).

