#### Adverse events

A risk assessment of the PD COMM trial has been performed with the SLT interventions considered to be of low risk. From the literature, the only reported AE associated with the interventions was a small increased risk of vocal strain or abuse; however, none were reported in the PD COMM Pilot trial. This risk will be minimised: speech and language therapists are trained to identify and rehabilitate vocal strain so, if present, the therapist will be able to identify and address it. No other risks are expected to arise from taking part in the trial. It is, therefore, reasonable to collect only targeted AEs.

For participants in either therapy arm, any vocal strain or abuse believed to be associated with treatment will be identified by the therapists at the participants’ therapy session and will be reported in the AE log.

In all trial arms, BCTU will also check the participant-reported resource usage form to ensure that no vocal strain or abuse has occurred following participants reporting out-patients appointments with ear, nose and throat (ENT) specialists. At the 12-month clinical visit, the medical professional will also check whether any AEs have occurred since entering the trial.

Serious adverse events (SAEs) are events that cause death, are life-threatening, require or extend an existing hospitalisation, result in persistent or significant disability or incapacity; or, are otherwise considered medically significant by the investigator. SAEs that are not related to vocal strain or abuse are excluded from expedited notification during the course of the trial and will be collected in the resource usage and 12-month clinical case report form (CRF).

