**Assessments**					
Baseline case report form		✓			
VHI; PDQ-39; QASD; EQ-5D-5 L; ICECAP-O		✓	✓	✓	✓
Resource Usage Questionnaire			✓	✓	✓
Global rating score (Transition item)			✓		
PDQ-Carer		✓	✓	✓	✓
Adverse event log			✓^c^		
12-month case report form					✓

^a^Following each therapy session for participants in the two SLT treatment arms only

^b^Completed at home by the participant as recommended in their SLT therapy session

^c^Only required for participants randomised to a treatment arm

Key: *EQ-5D* EuroQol 5-dimension, 5-level questionnaire, *ICECAP-O* ICEpop Capabilities Measure for Older Adults, *QASD* Questionnaire on Acquired Speech Disorders, *PDQ-39* Parkinson’s Disease Questionnaire-39, *SLT* Speech and Language Therapy, *VHI* Voice Handicap Index

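### The therapy-versus-control adverse event comparison confounds harm with ascertainment, because the therapist log adds events only in the therapy arms (minor point)

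*Protocol article*

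**What the plan says.** All references are to the protocol article.

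- **Analysis (Secondary outcome analyses).** "Adverse events and safety data will be summarised descriptively by treatment arm". The section adds that few AEs are expected, and then that "the number of participants reporting an AE will be compared using a chi-squared test, with relative risks and 95% confidence intervals reported", with a bracketed qualifier, where appropriate, at the end of the sentence. Neither the arms nor the AE sources entering the test are restricted.
- **Therapist route (Adverse events).** "For participants in either therapy arm, any vocal strain or abuse believed to be associated with treatment will be identified by the therapists" at therapy sessions and entered in the AE log.
- **Who has a log (Table 2, footnote c).** "Only required for participants randomised to a treatment arm".
- **Routes for every arm (Adverse events).** "In all trial arms, BCTU will also check the participant-reported resource usage form to ensure that no vocal strain or abuse has occurred", prompted by reported ENT out-patient appointments. Then: "At the 12-month clinical visit, the medical professional will also check whether any AEs have occurred since entering the trial". Serious events unrelated to vocal strain are taken from the resource-use form and the 12-month case report form (CRF), neither of which is limited to the therapy arms.
- **Contrasts and threshold.** Methods/design lists three pairwise comparisons, two of them against control. Statistical analysis sets significance at p < 0.01 and analyses participants as randomised.

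**The concern.** A between-arm relative risk can be read as a safety estimate only if an event has a similar chance of being counted in each arm. Here the therapy arms have the common routes plus a therapist who is trained to recognise strain and logs it at therapy sessions. Control participants have the common routes alone, and by default no therapist contact for 12 months. The log's attribution criterion also has no counterpart for someone receiving no therapy. Footnote c turns on the randomised arm, so a control participant who does receive SLT still has no required log.

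At stake is the reading of a secondary safety result: therapy could appear to carry more risk than control partly because strain is looked for more closely there.

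**Working it through.** **1. Routes by arm**

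| Route | LSVT LOUD | NHS SLT | Control | Where stated |
|---|---|---|---|---|
| Therapist log, treatment-attributed strain | yes | yes | no | Adverse events; Table 2, footnote c |
| Resource-use form, ENT prompt | yes | yes | yes | Adverse events |
| 12-month check | yes | yes | yes | Adverse events |

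The routes differ only in the two contrasts with control.

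**2. What the relative risk then estimates**

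Let c_T and c_C be the probabilities that a therapy or control participant has an AE found by a common route. Let l be the probability that a therapy participant has an AE found by the log alone. Then

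observed RR = (c_T + l) / c_C = c_T/c_C + l/c_C.

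If the common routes find equal proportions, RR = 1 + l/c_C. Since l cannot be negative, the log can only raise the ratio. Part of l is real harm from therapy; part is strain that would have gone unrecorded without a therapist. The planned test cannot separate the two.

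**3. Figures available**

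The article gives no AE rate, no detection rate and no planning figure for this comparison. It says that no vocal strain or abuse was reported in the pilot. The arm size reproduces: 163 / (1 − 0.10) = 181.1, rounded up to 182, and 3 × 182 = 546. I use 182 per arm below.

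**4. How few log-only events would matter**

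Take k participants with an event in a therapy arm and none in control, with p̄ = k/364. The Pearson statistic without continuity correction is (k/182)² / [p̄(1 − p̄) × 2/182].

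- k = 6: 0.001087 / 0.000178 = 6.10, p = 0.0135.
- k = 7: 0.001479 / 0.000207 = 7.14, p = 0.0075.

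Seven events seen only through the log would cross the trial's threshold. The expected number with an event is then only 3.5 per arm, so the chi-squared approximation is weak, and the relative risk is undefined with a zero denominator.

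**5. Illustration (risks and detection rates are assumptions)**

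Assume the same true risk in both arms, with 0.90 of events detected in a therapy arm by all routes together and proportion d in control. Expected RR is about 0.90/d. The last three columns give the exact probability that the Pearson test yields p < 0.01 at 182 per arm.

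| d | Expected RR | True risk 2% | True risk 5% | True risk 10% |
|---|---|---|---|---|
| 0.90 | 1.0 | 0.0040 | 0.0080 | 0.0098 |
| 0.60 | 1.5 | 0.0061 | 0.0251 | 0.0655 |
| 0.45 | 2.0 | 0.0099 | 0.0598 | 0.1882 |
| 0.30 | 3.0 | 0.0167 | 0.1405 | 0.4407 |

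These rows are not predictions. Equal true risk means that none of the strain is caused by therapy, and a log confined to treatment-attributed strain would leave much of that out. Detection in the therapy arms would then be below 0.90 and the distortion smaller than shown.

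**The case against.** The defence is substantial. The analysis is descriptive first, the comparison carries a qualifier, and an article may leave the choice of AE sources to the full protocol or the analysis plan. The trial is judged low risk, collects only targeted AEs, and excludes people with a history of vocal strain. At a true risk of 2%, false significance stays at or below 0.0167 in the illustration. The attribution criterion works against the bias for background strain.

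Most of this stands as a limit on size. It does not remove the problem. The qualifier comes with no criterion and follows a remark about few events, so it reads most naturally as a provision for sparse data. The descriptive summary does not replace the test. As written, the article states a comparison without limiting it to events that all arms could contribute.

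Three stronger readings are tempting, and the article does not support them:

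- **That the comparison measures detection and not harm.** Both all-arm routes let control events be counted, so harm is mixed with ascertainment but not absent.
- **That LSVT LOUD versus NHS SLT is biased in the same way.** Both arms share the log and its criterion. The 16 sessions against a pilot median of six belong to the randomised treatments, and risk per participant randomised is the intention-to-treat quantity.
- **That a particular inflation factor can be quoted.** Any such figure rests on detection rates the article does not give.

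**Conclusion.** The point holds for LSVT LOUD versus control and NHS SLT versus control. If the test pools all AE sources, as the wording allows, the relative risk confounds harm with ascertainment, and the log can push it only towards more events under therapy. This rests on the log being confined to the therapy arms, which the article states, and on log events entering the test, which it does not exclude.

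The magnitude is unknown. It ranges from negligible, if events are as rare as the pilot suggests, to appreciable if strain is common and detection very unequal. This is a minor point on a secondary safety analysis.

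**What to change.** Amend the AE analysis wording as follows:

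1. Limit any test or relative risk against control to AEs found through the all-arm sources (resource-use form and 12-month CRF). An event found both by the log and by one of these counts through the common source.
2. Report therapist-log events separately and descriptively for the two therapy arms. Confine any comparison of them to LSVT LOUD versus NHS SLT, per participant randomised. A rate per session is optional.
3. State in the results that ascertainment differed by arm.

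This needs no new data collection. The log, the resource-use questionnaire and the 12-month CRF are separate instruments in Table 2, so the source of each event should be identifiable; the article does not say so outright, and this should be confirmed with the trial database.

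There are two costs. Fewer events enter the formal comparison, and mild therapy-related strain seen only by therapists appears only in the descriptive report. The common routes are also not perfectly neutral: a participant told of strain by a therapist may be more likely to see ENT or to mention it at 12 months. The change reduces the bias but may not remove it.

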### Planned subgroup analyses

Subgroup analyses will be performed for the primary outcome to assess whether there are differences in treatment effect by the minimisation variables: age; baseline voice severity (as measured by VHI); and PD severity (as measured by Hoehn and Yahr). The trial is not powered to detect differences in treatment effect in these subgroups and, therefore, these analyses will be treated as purely hypothesis generating.

#### Health economics analysis

The economic evaluation will estimate the cost-effectiveness of LSVT LOUD® or standard NHS SLT compared to no SLT treatment (control) in PD. The base-case economic evaluation will be undertaken from the UK NHS and personal social services (PSS) perspective, with further analysis from a broader societal perspective, over 12 months’ follow-up.

A cost-effectiveness analysis will use the primary outcome (VHI) to calculate the cost per unit improvement in VHI score, and a cost-utility analysis will use responses from the EQ-5D-5 L to calculate cost per quality-adjusted life year (QALY) gained. Resource-use data will be collected on PD-related medication, primary care and secondary care healthcare utilisation, including the use of therapy services, and use of social services including formal care. Further information will be collected on time off work, participant out-of-pocket costs and costs incurred by informal carers, in order to inform analysis from a societal perspective. The cost of delivering the LSVT LOUD® intervention and NHS SLT, including length and number of sessions and any training required will be determined within the trial. Data will be collected using a participant-completed resource utilisation questionnaire (at 3, 6 and 12 months) and the therapist-completed initial interview logs and treatment record forms. Unit costs from routine sources will be applied to resource-use data [46, 47]. Health-related quality of life will be assessed using the EQ-5D-5 L [41] collected at baseline, 3, 6 and 12 months. The crosswalk value set will be applied to patient responses to obtain utility scores, in line with current NICE recommendations and QALYs calculated using the ‘area under the curve’ approach. The ICECAP-O [42] will also be used to capture changes in participants’ capabilities, allowing a broader assessment of benefits to patients.

Incremental cost-effectiveness and cost-utility analyses will be undertaken to estimate the incremental cost per unit of outcome gained, adjusting for baseline covariates. Two sets of comparisons will be undertaken. In line with convention, strategies will be ordered from least to greatest cost, with each strategy compared against the next more costly strategy, and strategies which are dominated or extendedly dominated subsequently excluded. A separate analysis will also consider the three pair-wise comparisons as specified in the statistical analysis. Both deterministic and probability sensitivity analysis will be undertaken and cost-effectiveness acceptability curves will be produced to reflect the probability the intervention will be cost-effective at different willingness to pay thresholds, in terms of cost per unit of outcome gained.

#### Dissemination

The trial results will be disseminated widely through scientific conferences and peer-reviewed publications. Collaborators will be informed of the trial results at a national trial results meeting and participants will be sent a newsletter thanking them for their support and informing them of the trial results. We will also use social media and work with the Universities media services, National Institute of Health Research (NIHR) Health Technology Assessment (NIHR HTA) dissemination services and the Parkinson’s UK charity to broaden our dissemination to key stake-holders and the wider community.

## Discussion

The PD COMM trial is already the largest trial of SLT in PD to date (as of 10 September 2019, 329 participants have been recruited). It will provide robust evidence as to the effectiveness and cost-effectiveness of two types of SLT for people with PD enabling them, their clinicians and NHS decisions-makers to make informed choices.

There will also be benefits beyond the immediate trial results: the group has developed a research network of speech and language therapists in 42 sites around the UK, participated, and provided training in, LSVT LOUD® (courtesy of [name]), trials, other aspects of PD and research into SLT and information on best practice. This project will lay the foundation for further trials in SLT and lower the barriers to future research. Furthermore, we will develop a clear understanding of the range of SLT practice around the UK for people with speech or voice problems as a consequence of PD, in terms of dosage, content and availability.

## Trial status

Protocol version number and date: version 4.0 (14 November 2018).

The first participant was recruited into the trial on 11 October 2016. Recruitment is ongoing with an expected recruitment end date of 30 November 2020.

## Data Availability

Following the publication of the main trial results anonymous data sets will be available on an individual case-by-case basis in accordance with the University of Birmingham, Birmingham Clinical Trials Unit’s Standard Operating Procedures with agreement from [name] and King’s College, London.

## Abbreviations

AE: Adverse event
ACC: Augmentative and alternative communication
BCTU: Birmingham Clinical Trials Unit
ENT: Ear, nose and throat
ICECAP-O: ICEpop Capabilities Measure for Older Adults
ISRCTN: International Standard Randomised Controlled Trials Number
LSVT LOUD®: Lee Silverman Voice Treatment
MCID: Minimal clinically important difference
CETI-M: Modified Communications Effectiveness Index
PD: Parkinson’s disease
PDQ-39: Parkinson’s Disease Questionnaire-39
PIS: Patient information sheet
RCTs: Randomised controlled trials
SAE: Serious adverse event
SPL: Sound pressure level
SLT: Speech and Language Therapy
VRQOL: Voice-related Quality of Life
VHI: Voice Handicap Index
